**Fig. 3 Fig3:**
[figure not shown]
CONSORT flow diagram

### Methods for each study aim

*Aim 1: To refine strategies to integrate cervical cancer screening and treatment of cervical precancers within existing comprehensive HIV treatment programs*. This has been described above in the EPIS preparation phase, and the findings are included in Tables 1 and 2.
*Aim 2: To determine the comparative effectiveness of the Core vs Core+ Implementation Strategies on CSST*

### Study population

To be eligible for enrolment into the trial, a woman must meet all the following criteria:Be between 25 and 63 yearsHave been diagnosed with HIVEnrolled into HIV care in the sites

WLHIV will not be eligible to be enrolled into the trial if they have been previously diagnosed with preinvasive or invasive CC, received CC screening at any time within the previous 12 months, or are not willing to participate in the study procedures.

### Recruitment and retention

The medical records team will provide a list of potentially eligible WLHIV based on the eligibility criteria. The eligible WLHIV will be approached by the SRCs for recruitment into the study. For those who indicate interest, the SRCs will provide more details about the study, after which signed informed consent will be obtained electronically using REDCap. The consent forms will be read to all the participants in the English language. When there is a language barrier, the multilingual SRCs will interact with the potential participants in their local dialect. At enrollment, appointments for their next visit (data collection) will be scheduled.

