**Fig. 1 Fig1:**
[figure not shown]
EPIS framework activities and outer/inner contexts

Prior to grant submission and funding, we completed the *exploration phase* [48] where we used survey and modified nominal group techniques (NGT) [51] to conduct a rapid and facilitated implementation mapping [52] exercise. Collaborators identified and ranked barriers and identified, selected, and ranked implementation strategies starting with the Expert Recommendations for Implementing Change (ERIC) [53] and other identified additional strategies. The final set of strategies were selected to address the barriers to integration of CCST into HIV treatment programs to form the Core IS. Stakeholders identified two additional strategies to be included in the Core+ IS condition [48].

In the *preparation phase*, we refined the IS and convened implementation resource team (IRT) [54] meetings to further reflect on the refined Core and Core+ IS fit with local context. Implementation resource teams were first conceptualized and tested in the dynamic adaptation process model and the Interagency Collaborative Team model for scaling up evidence-based practices [54, 55]. The IRT for this study is a community-engaged co-creation collaborative comprising the research team and the doctors and nurses from the study sites. Twelve site research coordinators (SRCs) were also recruited and trained during this phase.

The process of refinement of our proposed implementation strategies occurred in two phases. In the first phase, the research team developed an IS table which included the identified implementation determinants (barriers/facilitators), the initially proposed IS for each determinant, a definition of each IS, the population targeted by the IS, the proposed actions for the IS, and the responsible person(s) for these proposed actions. For each IS, we discussed its feasibility and importance in addressing the implementation determinant based on the IRT’s current knowledge of the context in the implementation sites. For each IS that IRT identified as not being the most feasible or important to address the implementation determinant, we selected another IS from the same category in the ERIC grouping of implementation strategies [53], and we included some strategies not included in ERIC. The refined strategies are shown in Table 1.

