#### Site selection

The study will leverage the 21 comprehensive HIV treatment sites across the six geopolitical zones of Nigeria that have been designated as Nigeria Implementation Science Alliance (NISA) Model Innovation and Research Centers (NISA-MIRC) [65]. The NISA-MIRC sites are part of the ICON-3 Practice-based Research Network which is made up of the 21 NISA-MIRCs and the 6 Regional Centers of Excellence. The NISA-MIRCs have over 60,000 WLHIV in care who are eligible for enrollment into clinical trials and other implementation research studies [65]. Our proposed study will be anchored at 12 sites (see Figure 2 and Additional file 1) from the 21 NISA-MIRCs. The criteria for selection were based on the following: (1) geographical spread (two sites per region), (2) highest proportion of consented WLHIV for enrolment into clinical trials and other implementation research studies, and (3) match of the same type of site per region (secondary or tertiary).

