#### Randomization

The unit of randomization will be the sites. Each site represents a cluster in the randomization representing the clinic site and the WLHIV receiving treatment at the site. We will conduct simple random allocation with the sites randomized to either the Core or Core+ IS. There are six geographic regions in Nigeria, and sites will first be matched by region, and then each site in a matched pair will be randomized to Core or Core+ IS. A random number generator will be used to assign the sites. A flow diagram for the randomization and intervention allocation is shown in Figure 3. The healthcare workers and the patients will be blinded to whether their sites are allocated to the core package of IS or an enhanced package of IS.

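### The stated recruitment procedure does not protect the primary screening-rate comparison from differential recruitment by arm

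*Protocol article*

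**What the plan says.** All references are to the protocol article.

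- **Unit of randomisation.** Randomization makes the site the unit, with sites paired by region and one of each pair assigned to each package.
- **Who recruits.** Under Recruitment and retention, "The medical records team will provide a list of potentially eligible WLHIV based on the eligibility criteria". Then "The eligible WLHIV will be approached by the SRCs for recruitment into the study", and the coordinators explain the study to interested women and obtain individual consent. The coordinators are a study role. In the account of the preparation phase, "Twelve site research coordinators (SRCs) were also recruited and trained during this phase".
- **Who is blinded.** Randomization states: "The healthcare workers and the patients will be blinded to whether their sites are allocated to the core package of IS" or to the enhanced one. Coordinators are not mentioned.
- **Who is excluded.** Study population excludes, among others, women who "are not willing to participate in the study procedures".
- **How many.** Sample size and power calculation plans 200 women at each of 12 sites. Site selection gives the wider pool across 21 centres: "The NISA-MIRCs have over 60,000 WLHIV in care who are eligible for enrollment into clinical trials and other implementation research studies".
- **What is measured, and in whom.** Schedule of measurement assesses each participant for receipt of screening 12 months after enrolment.
- **What differs between arms.** Table 2 adds two strategies in Core+: community engagement sessions at HIV support-group meetings, and a patient-held smartcard that is scanned at study visits and linked to appointment reminders.
- **How imbalance is handled.** Data analysis and the covariate pre-screening section test baseline variables and consider those that differ, or that predict the outcome, as covariates.

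**The concern.** Randomising sites balances the arms only up to the point where individual women enter. If women are recruited after the arm is known or can be guessed, who is approached and who agrees can depend on the arm. Willingness to take part in a screening study is close to the outcome itself, so a modest difference in the kind of woman enrolled passes directly into the difference in screening rate.

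Three features together create the exposure:

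1. The recruiter is based at the site and is not among those stated to be blinded.
2. The Core+ components can be seen at the site.
3. No rule fixes which listed women are approached, or in what order, on the way to 200.

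None of the planned analyses closes this gap. Intention-to-treat protects the comparison only after enrolment. The random site intercept deals with clustering, not with a shift common to one arm. Covariate adjustment reaches only what was measured.

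**Working it through.** **1. Reproducing the stated power.** Inputs from Sample size and power calculation: 14% v 34%, 6 sites per arm, 200 women per site, two-sided 0.05, ICC 0.02 to 0.07. The design effect is 1 + 199 × ICC. The effective number per arm is 1,200 divided by the design effect. The standard error is √[(p₁(1−p₁) + p₂(1−p₂)) / effective n], and power comes from a noncentral t with 2 × (6 − 1) = 10 df.

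| ICC | Design effect | Effective n per arm | Power | Stated |
|---|---|---|---|---|
| 0.02 | 4.98 | 241.0 | 99.7% | > 99.9% |
| 0.06 | 12.94 | 92.7 | 84.0% | 84% |
| 0.07 | 14.93 | 80.4 | 78.6% | 78.6% |

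The method matches at ICC 0.06 and 0.07 and is very close at 0.02, so it is used again in step 4.

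**2. How much of a site's pool is enrolled.** 60,000 / 21 = 2,857 women per centre on average, and 200 / 2,857 = 7.0%. This is the share enrolled. The share approached is larger if any woman declines. The pool is women eligible for research in general, before this trial's age, prior-diagnosis and recent-screening exclusions. The sizes of the 12 chosen sites are not given in the text shown, and one selection criterion was a high proportion of consented women. Assumed pools give this range: 200 / 5,000 = 4.0% and 200 / 1,500 = 13.3%.

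**3. An assumed route to a spurious difference.** None of these values comes from the documents except the 14%. Suppose 30% of a site's women are engaged with care and 30% of them get screened. For an overall rate of 14%, the others must be screened at (0.14 − 0.30 × 0.30) / 0.70 = 7.14%. If engaged women form 50% of those enrolled in Core+ and 30% in Core, the Core+ rate is 0.50 × 0.30 + 0.50 × 0.0714 = 18.6%, against 14%. The gap is 4.6 points with no true effect.

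**4. Chance of p < 0.05 with no true effect.** The calculation of step 1 is used with 14% in Core and 14% plus the shift in Core+. For 5 points at ICC 0.02, SE = √[(0.14 × 0.86 + 0.19 × 0.81) / 241.0] = 0.0337, so the noncentrality is 0.05 / 0.0337 = 1.48. The critical value is 2.228.

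| Spurious shift (points) | ICC 0.02 | ICC 0.06 |
|---|---|---|
| 0 | 5% | 5% |
| 2 | 9% | 6% |
| 4.6 | 23% | 12% |
| 5 | 27% | 13% |

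These are two-sided rejection rates.

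**The case against.** The strongest reply is that this reads conduct into silence.

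- **Coordinator choice.** A reader might infer that coordinators pick which women to approach. The text does not say so. The list is made by the medical records team, and the sentence on approach can be read as covering every listed woman. This stands. Selection is only implied, by a target of 200 from a pool that probably runs to thousands.
- **The 7%.** A reader might take it as the fraction approached at the trial sites. It is an enrolled share at a 21-centre average, before exclusions. This also stands, but assumed pools of 1,500 to 5,000 still leave most women unenrolled.
- **Timing and awareness.** Bias of this kind needs recruiters who know or can guess the arm. The text fixes neither the order of randomisation and enrolment nor what coordinators know. They might be counted as healthcare workers, and the flow diagram and assessment figure are not shown. This stands, so actual bias cannot be asserted. Blinding is hard to rely on, however, when one arm has smartcards and support-group sessions.
- **The willingness exclusion.** It applies to both arms and creates no difference by itself. It matters only if the arm influences who agrees.
- **Condensation.** An article may leave draw order and approach logs to a fuller document. That is fair, and one sentence would settle the point if they are there. But the article sets out recruitment step by step and makes a blinding claim, and as stated those steps leave the selection unprotected.
- **The illustration.** The engaged-mix values are assumed, and even 5 points is a quarter of the planned 20-point difference. The figures show sensitivity and are not a forecast.

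**Conclusion.** The concern holds as an exposure and not as demonstrated bias. The stated procedure measures the primary outcome only in individually recruited women. It gives no sampling order, does not place enrolment before allocation is known, and does not name the recruiters among those blinded. Differential recruitment by arm is therefore possible, and adjustment for measured covariates cannot remove a difference in unmeasured willingness.

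The size is unknown. With no true effect, shifts of 2 to 5 points would raise the two-sided error rate from 5% to about 9–27% at ICC 0.02 and about 6–13% at ICC 0.06. This rests on the assumed shifts, a 14% Core rate, 200 women at each of 6 sites per arm, and a t reference with 10 df. The documents do not support saying that coordinators select women, that they know the allocation, or that the result will be biased. Confidence is medium, and the change should be made because it protects the primary comparison at little cost.

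**What to change.** 1. Freeze each site's medical-records list and put it in a centrally generated random order. Coordinators approach women in that order until 200 are enrolled.
2. Complete enrolment and baseline data at both sites of a pair before their allocation is disclosed to site staff and coordinators. If allocation is already known, keep the random order and use identical consent text in both arms.
3. Report the numbers approached, refused and enrolled by arm.
4. State in the blinding paragraph whether coordinators know the allocation, and when enrolment falls relative to its disclosure.

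**Cost.** Central staff must generate 12 ordered lists and hold back the allocation. The faster site of a pair waits a short time for the other, and some women high on a random list will be harder to reach. The sample size and the analysis model do not change. If the full protocol already contains these safeguards, a sentence saying so is enough.

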### Data collection

Sociodemographic and baseline data will be collected from the enrolled participants who will also be followed up to assess the outcomes of interest using structured follow-up questionnaires in addition to their electronic medical records. Data on potential determinants and mechanisms will be obtained from the healthcare providers, using the following validated instruments (see Additional file 2).

#### Organizational Readiness for Implementing Change (ORIC)

The ORIC assesses organizational readiness through two subscales, change commitment, and change valence. The ORIC has established high inter-item consistency and inter-rater reliability for both subscales [66]**.**

#### Implementation climate measure (ICM)

The six-item ICM has three subscales that assess perceptions of the degree to which a specific evidence-based practice (EBP) or innovation is expected, supported, and rewarded (i.e., recognition) in a clinic or organization [67]. The ICM has established strong psychometric properties.

#### Measure of innovation-specific implementation intentions (MISII)

The MISII is a three-item pragmatic measure of direct service providers’ (e.g., physicians, nurses, providers) intentions to engage with and use a specific innovation such as CCST [68]. The MISII has strong psychometric properties.

#### Self-Efficacy/EBP Beliefs Scale

This scale assesses the perceived value of the EBP and self-efficacy regarding the ability to implement the EBP. We will use the seven items that directly assess self-efficacy and we will tailor them to refer to CCST [69]**.**

#### Outcome measures

The measures for the implementation and clinical outcomes and the potential mechanisms are summarized in Table 3.

### Sample size and power calculation

We examine the sample size for the primary implementation outcome of “reach,” indicated by the CC screening rate in WLHIV. Based on preliminary data from previous studies, we assumed a conservative screen rate of 14% in the core implementation strategy group [70]. We plan to enroll 12 sites (6 sites per intervention group). Hade et al. [71] reported the range of intraclass correlation (ICC) fall in 0.02–0.07 in the group-randomized breast and CC screening studies. We performed a sensitivity analysis by assuming a range of ICC of 0.02–0.07 for site cluster effect on the outcome and a feasible sample size of 200 subjects per site. We estimated that we could achieve at least 80% power for ICC of 0.02–0.06 (84% for *ICC* = 0.06 and > 99.9% for *ICC* = 0.02) to detect a minimum improvement of 20 percentage points in screening rate (that is, 34% screening rate) in Core+ group using a two-sided type I error of 0.05, and we could still achieve 78.6% power for *ICC* = 0.07. The 34% screening rate is achievable and a conservative estimate for the Core+ group based on our prior related work [61]. The power analysis was conducted using the statistical software R package *cluster Power* [72].

### Data analysis

Preliminary analyses will begin with an examination of the distribution of variables to assess and describe their characteristics (means, standard deviations, quartiles, ranges, frequencies, and percentages) for overall and for Core and Core+ groups separately and to allow assessment of randomization. Randomization will be tested by performing a series of Wilcoxon rank-sum tests for continuous variables and chi-square (or Fisher’s exact) tests for categorical variables to compare the groups on baseline demographic and clinical variables. Variables on which the groups differ initially will be explored as covariates in subsequent analysis. Intent-to-treat analysis will be conducted as the primary analysis. All estimates (point estimates and 95% confidence intervals) for the study outcomes will be adjusted by the cluster effect of clinics as described below.

The screening rate (primary outcome) will be summarized by frequency and proportion. A generalized linear mixed-effect model (GLMM) [73] with a binomial link will be used to examine the difference in screening rate (reach outcome) between Core and Core+. A random intercept will be included in the model to account for the cluster effect of the site. Multivariable random effects models will be used to examine the impact of covariates on estimated intervention effects. The GLMM will be also used to compare secondary outcome measures related to adoption, implementation strategies fidelity, and clinical intervention fidelity between two intervention groups, with a binomial link for a binary outcome and a Gaussian link for a continuous outcome. The ICM, MISII, and Self-Efficacy/EBP Beliefs Scale data collected from providers will also be analyzed similarly using the GLMM.

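### The primary mixed model for 12 sites names no small-sample method, although two of the three stated powers assume one; a large-sample test could run at about 7.5% to 11% instead of 5%, depending on regional variation

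*Protocol article*

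**What the plan says.** The Data analysis section (Aim 2) sets a generalized linear mixed model with a binomial link as the primary analysis of screening rate. It handles clustering this way: "A random intercept will be included in the model to account for the cluster effect of the site". The same model type is carried over to secondary outcomes and provider scales. The section does not name the test (Wald or likelihood ratio), the estimation method, the reference distribution or the degrees of freedom. The model has no region or pair term, although the Randomization section matches sites by region and allocates within each matched pair.

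The Sample size and power calculation section gives 12 sites, six per arm, and "a feasible sample size of 200 subjects per site". On the Core rate it says "we assumed a conservative screen rate of 14% in the core implementation strategy group", and the aim is "to detect a minimum improvement of 20 percentage points in screening rate (that is, 34% screening rate) in Core+ group". The test level is 5%, two-sided. The ICC range is 0.02 to 0.07. The stated powers are above 99.9% at ICC 0.02, 84% at ICC 0.06 and 78.6% at ICC 0.07.

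**The concern.** The arm effect is a between-site contrast, so its precision rests on a between-site variance estimated from 12 sites, with 10 df left after two arm means. Two things then go wrong with a routine large-sample fit. Maximum likelihood underestimates that variance, in effect dividing by 12 where 10 is needed. A normal or chi-square reference then treats the estimate as known. Both make the test too liberal and the interval too narrow.

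The power section appears to allow for this at its two higher ICC values, and the analysis section does not carry the allowance over. If the gap is filled by default software output, the test performed is not the one that was powered. The primary p-value and confidence interval for Core+ against Core are at stake.

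**Working it through.** **Stated power.** All inputs come from the sample size section: rates 0.14 and 0.34, 200 women per site, six sites per arm (1,200 women per arm), two-sided 0.05.

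- Variance sum: 0.14 × 0.86 + 0.34 × 0.66 = 0.3448.
- Design effect: DE = 1 + 199 × ICC.
- SE = √(0.3448 × DE / 1200); noncentrality = 0.20 / SE.

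| ICC | DE | SE | Noncentrality | Power, t(10) | Power, normal | Stated |
|---|---|---|---|---|---|---|
| 0.02 | 4.98 | 0.0378 | 5.29 | 99.7% | 99.96% | >99.9% |
| 0.06 | 12.94 | 0.0610 | 3.28 | 83.97% | 90.7% | 84% |
| 0.07 | 14.93 | 0.0655 | 3.05 | 78.56% | 86.3% | 78.6% |

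The normal version with pooled variance gives 89.7% and 85.0% at ICC 0.06 and 0.07, so it does not match either. The two figures that decide the design fit t on 10 df (critical value 2.23). The figure at ICC 0.02 fits the normal reference and not t, though the gap is small.

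**Closed-form size of a large-sample test, no variation shared within regions.**

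- Unbiased variance, normal reference: 2 × P(t₁₀ > 1.96) = 7.8%.
- Maximum-likelihood variance, normal reference: 2 × P(t₁₀ > 1.96 × √(10/12)) = 2 × P(t₁₀ > 1.79) = 10.4%.

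**Simulation under the null, no variation shared within regions.** The setting was 12 sites of 200 women, a common rate of 14% (24% as a check), and ICC 0.02, 0.05 and 0.07. Site effects were logistic-normal or beta. The random-intercept logistic model was fitted by maximum likelihood with adaptive quadrature in 5,000 trials per setting (Monte Carlo SE about 0.4 points). The REML-type fits used 4,000 trials per setting at a rate of 14%.

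| Test | Rejection rate at nominal 5% |
|---|---|
| ML Wald z | 9.5-10.9% |
| Likelihood ratio | 7.6-8.5% |
| REML-type, z | 7.4-8.2% |
| ML Wald with t(10) | 6.3-7.3% |
| REML-type, t(10) | 4.4-5.1% |
| Site-level t-test, 10 df | 4.3-5.5% |
| Paired site-level t-test, 5 df | 4.1-5.4% |

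A separate run of 2,000 trials per setting, with rates of 14% to 34%, gave 8.8-11.0% for ML Wald z. Together the runs support about 9-11%. Putting t(10) on the ML fit corrects only part of the error.

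**With variation shared within regions.** The document gives no share, so it was varied as an assumption (rate 14%, ICC 0.05, same model without a region term).

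| Share of site variance that is regional | ML Wald z | Likelihood ratio |
|---|---|---|
| 25% | 7.1% | 5.3% |
| 30% | 6.3% | 4.7% |
| 40% | 5.0% | 3.4% |
| 50% | 4.0% | 2.8% |
| 75% | 1.7% | 1.2% |

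**Power if the pairs are analysed.** With the same noncentralities and 5 df, and no precision gained from matching, power is 74.6% at ICC 0.06 and 68.7% at ICC 0.07.

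**The case against.** The strongest reply is that the article leaves the reference distribution open, and that such detail usually belongs in the analysis plan, which is not shown. A site random intercept is compatible with Kenward-Roger or Satterthwaite df, and a team that used t for power may well intend t for analysis. That stands as far as it goes: the document does not say that a large-sample test will be used, and a reader should not infer that it does. The point survives because the text fixes the primary model for 12 sites, two of its own powers hold only for a small-sample test, and the third (above 99.9% at ICC 0.02) fits the normal reference. The powers therefore do not settle which test is meant.

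A second reply is that matching by region was meant to capture shared variation, and that leaving the pairs out of the model then makes the test conservative. This also stands. At a share of about 40% the Wald test is near 5%, and beyond that it falls below. It limits the claim without removing it, because control of the error then depends on a share that nobody has stated.

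A reader might also infer that the planned covariate adjustment makes the error worse. The document does not say that those covariates are measured at site level, and no such adjustment was simulated, so that is not claimed.

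**Conclusion.** The concern holds conditionally. The primary analysis has no stated small-sample method for 12 sites, while the powers of 84% and 78.6% need one. If a large-sample test is used and little site variation is shared within regions, the true error is about 7.5-8.5% (likelihood ratio or REML-type z) to about 9-11% (ML Wald z). If about 40% or more of the site variance is regional, the same unpaired model is at or below 5%.

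It is tempting to conclude that a false claim for Core+ is about twice as likely as stated. The document does not support that without conditions: it needs the ML Wald z test, which is not named, and almost no shared regional variation, for which no figure is given. The defensible conclusion is that the plan as written cannot show that its 5% test is a 5% test. The results rest on equal sites of 200 and on the stated ICC range; the shared-variance results rest on ICC 0.05.

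**What to change.** State that the primary p-value and 95% confidence interval use a small-sample method, and not large-sample Wald or likelihood-ratio inference. Either of these will do:

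- a REML-type fit of the mixed model with Kenward-Roger or Satterthwaite (between-within) df; or
- a t-based analysis of the 12 site-level summaries.

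Set the df together with the decision on the region pairs. If the analysis is unpaired, use 10 df; the stated powers at ICC 0.06 and 0.07 then stand, and the test is conservative if regions share much variation. If it is paired, use 5 df and restate power: about 74.6% and 68.7% at ICC 0.06 and 0.07 if matching brings no gain, and higher if it does. In either case, name the reference distribution behind the power figures and recompute the one at ICC 0.02, which is 99.7% with t on 10 df.

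The change costs a sentence or two and a software option. The downside is wider confidence intervals than a large-sample analysis would give and, if the pairs are analysed, a lower stated power.

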### Reach, Effectiveness, Adoption, Implementation, and Maintenance (RE-AIM)

We selected RE-AIM as our evaluation framework for assessing individual- and setting-level outcomes important to program impact and sustainment [56, 57]. As shown in Table 3, we address relevant RE-AIM constructs: Reach, Effectiveness, Adoption, Implementation, and Maintenance (also known as Sustainment) [56, 57]. In operationalizing these five dimensions, we adapted the metrics recommended by the Integrative Systems Praxis for Implementation Research (INSPIRE) model [58]. We defined the constructs as follows: reach (screening rate); clinical effectiveness (posttreatment screen negative); adoption (uptake of IS by study sites); IS fidelity (degree to which the IS occurred according to protocol); implementation clinical intervention fidelity (delivery of CC screening, onsite treatment, and referral according to protocol); and maintenance (or sustainment) (the degree to which integration of CCST continued).

**Table 3 Tab3:** Measures by EPIS phase and study aims

Aim	Construct	Measurement	Data source
EPIS preparation and implementation phases			
2	Reach (EPIS inner context)	•% WLHIV who had CC screening	Health records Participant survey
2	Effectiveness (EPIS inner context)	•% WLHIV treated for preinvasive cancer who had negative posttreatment follow-up screening	Health records Participant survey
2	Adoption	•% study sites that used AVIVA app to capture CC cases for real-time support •% study sites that participated in the periodic review training sessions on CCST •% study sites that initiated monthly educational meetings •% study sites that participated in the quarterly stakeholder meetings •% study sites that identified a referral coordinator to follow through with referred WLHIV with suspected cancer and ineligible lesions for treatment •% study sites that distributed flyers/leaflets/flipcharts on CCST in clinics •% study sites (Core+) that conducted HBI at support group meetings •% study sites (Core+) that captured CCST data of recruited WLHIV on smart card •% study sites (Core+) that send appointment reminders to patients using the mHealth platform	Survey Documented records
2	Implementation strategy fidelity	•(QUANT) 7 items (for Core) and 11 items (for Core+) with subscales, degree that components of each strategy were implemented in terms of adherence, exposure, quality, and engagement	Survey Documented records Periodic reflection

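### Adoption is one yes/no per site, so the planned GLMM with a random site intercept cannot estimate its arm effect; strategy fidelity (7 v 11 items) needs a common item set before arms are compared

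*Protocol article*

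**What the plan says.** All references are to the protocol article.

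- **Model.** The Data analysis section for Aim 2 sets out a GLMM with a random intercept for site for the primary reach outcome. It then extends the model: "The GLMM will be also used to compare secondary outcome measures related to adoption, implementation strategies fidelity, and clinical intervention fidelity". Binary outcomes get the binomial form and continuous outcomes the Gaussian form. The section also says that estimates for all study outcomes will be adjusted for clustering by clinic.
- **Adoption.** Table 3 lists nine measures, each a percentage of sites. Six carry no arm restriction, for example the percentage of "study sites that used AVIVA app to capture CC cases for real-time support". Three are marked as Core+ only, for example the percentage of "study sites (Core+) that conducted HBI at support group meetings".
- **Strategy fidelity.** Table 3 gives "7 items (for Core) and 11 items (for Core+) with subscales", drawn from survey, documented records and periodic reflection. It does not say which items the two arms share, or how many scores each site contributes.
- **Sites.** The sample size section says "We plan to enroll 12 sites (6 sites per intervention group". The Randomization section pairs sites by region and randomizes within each pair.

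**The concern.** A random site intercept separates variation between sites from variation within them. Where the outcome is itself a property of the site and is recorded once, there is no variation within sites to separate. The fitted arm effect then depends on whatever intercept variance the software settles on. With only six sites per arm, an arm in which every site adopts, or none does, is also a realistic result for simple steps such as handing out leaflets, and the odds ratio then has no finite estimate. For the three Core+-only measures there is nothing in Core to compare with.

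For strategy fidelity the problem is different. The two arms answer instruments of different length, so a difference in an overall score mixes how well the same strategies were delivered with how the Core+-only items happened to score.

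In a hybrid type III trial, implementation outcomes are the main interest, and these are two of the named RE-AIM outcomes. If the method has to be changed after the model fails or gives an odd result, the replacement is chosen with the data in view.

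**Working it through.** **The plan's own figures.** No power or sample size is stated for adoption or fidelity. The stated power concerns reach only. It assumes 14% v 34%, 200 women per site, 6 sites per arm and a two-sided 0.05 level.

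- Design effect at ICC 0.07: 1 + 199 × 0.07 = 14.93. Effective n per arm: 1200 / 14.93 = 80.4.
- SE = √[(0.14 × 0.86 + 0.34 × 0.66) / 80.4] = 0.0655, so the noncentrality is 0.20 / 0.0655 = 3.05.
- Noncentral t on 10 df gives 78.6%, as stated. The same steps give 84.0% at ICC 0.06, as stated, and 99.7% at ICC 0.02 (stated as above 99.9%; a normal approximation gives 99.96%).

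These figures rest on many women per site. They do not carry over to an outcome with one value per site.

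**Adoption: identifiability.** With random-intercept SD σ and linear predictor b for an arm, the chance that a site adopts is π(b, σ) = ∫ expit(b + σz) φ(z) dz. With one value per site, the likelihood depends on b and σ only through π. For any σ some b reproduces the observed proportion, so the maximised likelihood is flat in σ. For 5/6 v 3/6 it is always

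5 ln(5/6) + ln(1/6) + 6 ln(1/2) = −0.9116 − 1.7918 − 4.1589 = −6.8623.

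| σ | Maximised log-likelihood | Odds ratio |
|---|---|---|
| 0 | −6.86225 | 5.0 |
| 0.5 | −6.86225 | 5.4 |
| 1 | −6.86225 | 6.7 |
| 2 | −6.86225 | 13.0 |
| 4 | −6.86225 | 69.2 |

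**Adoption: separation.** If an arm shows 6/6 or 0/6, its log-odds estimate is infinite. For the three Core+-only items, Core contributes either no data or a structural 0/6, so no arm effect can be estimated.

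**Adoption: what 6 v 6 can show.** An unpaired Fisher test gives 6 v 0: 2/924 = 0.002; 6 v 1 or 5 v 0: 12/792 = 0.015; 6 v 2: 30/495 = 0.061. That ignores the pairing. An exact sign test on the six regional pairs gives:

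- 6 v 0: six discordant pairs, all one way, 2 × (1/2)^6 = 0.031.
- 6 v 1 or 5 v 0: five discordant pairs, all one way, 2 × (1/2)^5 = 0.0625.

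So only 6 v 0 reaches 0.05. The documents give no expected adoption rates. With assumed true rates, and adoption independent within pairs, the power of the sign test is close to [p₁(1 − p₂)]^6:

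| Assumed rates | Fisher, unpaired | Sign test, paired |
|---|---|---|
| 90% v 50% | 6% | 0.45^6 = 0.8% |
| 100% v 50% | 11% | 0.50^6 = 1.6% |
| 100% v 30% | 42% | 0.70^6 = 12% |
| 95% v 20% | 54% | 0.76^6 = 19% |

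**Strategy fidelity.** At an equal average score per item, totals differ by 11/7 = 1.57 through item count alone. At most 7 items can be common, so at least 4 of the 11 Core+ items (36%) lack a Core counterpart. If all 7 are common and score the same average *a* in both arms, while the other 4 average *b*, the overall means still differ by (7a + 4b)/11 − a = 4(b − a)/11. With a single score per site, a Gaussian model sees only the sum of the intercept and residual variances, and the analysis reduces to a comparison of 12 site values.

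**The case against.** The best case for the plan has four parts.

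1. **Repeated or pooled records.** Some strategies run monthly or quarterly, so participation might be recorded repeatedly, or the six common items might be pooled into 72 values with a site intercept. Either would make the intercept estimable. Table 3 describes neither: it defines each measure as a share of sites, and several are one-off acts such as naming a coordinator.

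2. **The damage is narrower than a failed model.** The likelihood is flat in the intercept SD, so the likelihood-ratio test of arm and the fitted proportions do not change. This stands for data without separation. What is arbitrary is the conditional odds ratio, which is the effect measure that a logistic mixed model reports.

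3. **The Core+ items are already labelled.** A sensible reader would not compare them between arms. That is fair, but the analysis sentence makes no exception, and saying so costs nothing.

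4. **Scoring detail belongs in a SAP.** This is true of fidelity scoring as such. For adoption, however, the article names a method that does not fit its own outcome definition, which is not a detail left for later.

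A reader might infer that the fidelity comparison cannot work at all. The documents do not support that. Quarterly periodic reflections and survey sources make several scores per site plausible, and a Gaussian mixed model would then be estimable. Nor does the article say that raw totals will be compared. A reader might also assume that the 7 Core items sit inside the 11 Core+ items. That is likely, since Core+ adds strategies to Core, but it is not stated.

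**Conclusion.** The point holds for adoption. As Table 3 defines it, a GLMM with a site intercept cannot identify the intercept variance, and its odds ratio is not determined by the data (5.0 to 69.2 in the example). Separation is a real possibility on the common items, and three of the nine items have no comparator. This assumes one record per site per item, which is what the table's wording implies.

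For strategy fidelity the conclusion is milder: an overall total or mean on 7 v 11 items is not like for like, but a comparison on common items is workable once those items and the number of scores per site are stated.

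Only secondary outcomes are touched. The primary reach analysis and its power stand, and the GLMM suits clinical intervention fidelity, which is measured per woman, and the provider scales. The low power with 12 sites is not itself an error in an outcome that was never powered; it is a reason to describe rather than model. The point should be settled before outcome data are seen, but it does not threaten the trial's main conclusion.

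**What to change.** - Remove adoption from the GLMM sentence. Report each of the six common items as n/6 sites per arm, with at most an exact site-level test that respects the regional pairs.
- Describe the three Core+-only adoption items within Core+ alone.
- Restrict the between-arm comparison of strategy fidelity to items common to both arms, with the sponsor confirming which these are, and describe the Core+-only items separately. State how many scores each site contributes. If there is only one, use a site-level comparison.
- Keep the GLMM for participant-level and provider-level outcomes.

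The cost is wording in the analysis plan. No data collection, sample size or primary analysis changes. The downside is that the adoption comparison becomes openly descriptive, which is what 6 v 6 binary values can support.
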